### **3.1.5 Data analysis**

Data analysis will be performed using STATISTICA. Descriptive statistics will be used to describe the characteristics of health professionals, such as frequency and percentage, mean and standard deviation. Within-group analysis will be used. The dependent t-Test will be used to compare the means before and after intervention (training) to detect whether there are any statistically significant differences between two means. Data will be presented in forms of tables, Scatterplots, and graphs. The ICC for absolute agreement between the two raters' scores of the audit of patient records will be used to determine the reliability of the scoring. The accuracy of interpretation of folders will be indicated by a set of ten folders of patients discharged longer than 6 months ago, assessed by researcher and research assistant (s), Data entered and compared, discussion and consensus reached. A further 10 files assessed and this process will continue until 80% agreement is reached.

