##### **Patients' records**

- Medical records of patients who have been admitted to the orthopedic/surgical, medical and paediatric wards for at least five days.
- Medical records of patients who have been discharged.

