#### **Medical records**

A stratified sampling method will also be used to select the patients' medical records that will meet the inclusion criteria to be involved in the study. It is anticipated to have a maximum of 100 patients' records per hospital. In each hospital, 100 patients' records will be audited at each occasion: baseline, two months, four months, and six months after intervention. Only the records of

discharged patients will be audited as well the records of discharged patients during two months of data collection.

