#### **4.1 Data analysis**

Data will be entered into an Excel sheet by the researcher. For checking data entry error, ten percent of data will be double entered. The error of 5% will be set, above which the data would be double entered. Descriptive statistics will be used to describe the characteristics of the hospitals, health professionals and patients. Between-group analysis will be used to establish if the two sets of groups are equivalent at baseline and at two months, four months, and six months. Depending on the type of data and whether they are normally distributed, the chi-square, Mann-Whitney U or independent t-test will be used. Within group differences, to establish whether each group has altered over time will be done and will include McNemar's test, sign test and the dependent t-test. As cluster sampling has been done, multi-level regression analysis will be done to control for the effect of clustering. For comparison of the diagnosis categories of both groups will be performed using Chi-square test to ensure that there is no association between diagnosis and groups. If necessary, sub-group analysis will be performed post-hoc to explore the impact of diagnosis on the outcome measures. The data will be presented in forms of tables, Scatterplots, and graphs.

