#### **4.2 Ethical consideration**

Before conducting this study, required permission to conduct this study will be obtained from the relevant institutions and participants. Ethical approval will be sought from the University of Cape Town Institutional Review Board. For carrying out the study in Rwanda, the approval will be sought from National Health Research Committee (NHRC), and Rwanda National Ethics Committee (RNEC). The study will also need permission from the hospitals. A signed informed written consent (Appendix xii) will be requested from each participant. For reviewing patients' records for baseline data of discharged patients, the written consent will be requested from the hospital superintendent, but after the intervention (training), the informed consent form will be requested from patients or parents/guardians for having access to the folders once he/she will be discharged and assent will be obtained from minors who have the capacity to give assent.

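### Paired within-arm tests of change are not restricted to linked data: audited records come from different patients at each occasion, and a within-arm change does not estimate the effect of training

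*Combined protocol and SAP*

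**What the plan says.** Section 4.1 (Data analysis) has three layers: between-group tests at baseline and at two, four and six months; within-group tests; and a multi-level regression to deal with clustering. The within-group layer is described as "to establish whether each group has altered over time will be done and will include McNemar's test, sign test and the dependent t-test". No outcome is attached to any of these tests. The regression's outcome and terms for arm, occasion, arm-by-occasion and baseline are not given.

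The audit design is in Section 3.2.2.3 (Medical records): "In each hospital, 100 patients' records will be audited at each occasion: baseline, two months, four months, and six months after intervention". Eligible records are those of discharged patients (Section 3.2.2.1), and the sampling text refers to "the records of discharged patients during two months of data collection". Section 4.2 separates the two sources by consent. Before training: "For reviewing patients' records for baseline data of discharged patients, the written consent will be requested from the hospital superintendent". Afterwards, "after the intervention (training), the informed consent form will be requested from patients or parents/guardians", and Section 4.2.1 places that request on admission or during the stay.

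Section 3.2.2.2 makes the comprehensiveness score of the records part of the primary outcome. Section 4 also has staff knowledge and attitudes measured before and after training. Section 4.2.2 puts codes instead of names on the staff forms, but does not say that a person keeps one code across occasions.

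**The concern.** McNemar's test, the sign test and the dependent t-test all work on differences within linked pairs. A baseline record and a six-month record belong to different patients, so no such pair exists. An analyst following Section 4.1 literally would have to invent one.

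The second problem is separate and applies to staff forms as well. A test within one arm asks whether that arm changed. The trial asks whether trained hospitals changed more than comparators. Running the test once per arm invites the reading that training worked because the change was significant in one arm and not in the other. With four hospitals per arm and six months in which recording practice may shift everywhere, that reading could produce a claim of benefit with no effect behind it.

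**Working it through.** **The plan's own figure.** 20% of 40 hospitals = 8, and 8 × 100 = 800 records, as stated in Section 3.2.2.2. With four occasions the audits total 8 × 100 × 4 = 3,200 records. No alpha, power, SD or ICC is given, so no power statement can be checked. Every ICC and autocorrelation below is an assumption.

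**Are there pairs?** The baseline patients had already been discharged, so the superintendent consents for them. Post-training patients consent themselves during a later stay. Each occasion takes a new set of 100. A readmitted patient might appear twice, but no linkage is planned. The audits are repeated cross-sections.

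McNemar's test needs binary data. The yes/no instruments are the record checklists (Appendices v and vi), whereas the attitude form is an agreement scale and the knowledge form is an open case-study table. So McNemar's test points most naturally at the records.

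**Effect of arbitrary pairing.** Fixed artificial data were re-paired at random 5,000 times.

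- 30% against 37%, 400 records per occasion: McNemar p ran from 0.022 to 0.053 (unpaired chi-square 0.036).
- One hospital, 100 records per occasion, difference 0.28 SD: dependent-t p ran from 0.017 to 0.092 (independent t 0.049).

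The p-value depends on the matching. Without clustering, however, type I error stays near 5% (0.052 in 4,000 simulated trials).

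**One arm significant, the other not.** Suppose both arms change by the same amount and each within-arm test has power p. Then P(significant in the experimental arm only) = p(1 − p): 0.5 × 0.5 = 25%, and 0.8 × 0.2 = 16%. Simulation with a common shift of 0.14 SD gave 24% to 26%.

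**Pooled within-arm test with hospital-by-occasion variation.** Total variance is 1, with 4 hospitals × 100 records per occasion. C is the cluster autocorrelation: the correlation between a hospital's underlying levels at two occasions.

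- True variance of the arm's mean change: 2·ICC·(1 − C)/4 + 2(1 − ICC)/400
- Variance the test assumes: [2(1 − ICC) + 2·ICC·(1 − C)]/400
- Rejection rate: P(|Z| > 1.966/√ratio), where ratio is the first variance divided by the second

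| ICC | ratio at C = 0.8 | rejects, C = 0.8 | simulated, C = 0.8 | rejects, C = 0.5 |
|---|---|---|---|---|
| 0.01 | 0.00595/0.00496 = 1.20 | 7% | 8.2% | 11% |
| 0.05 | 0.00975/0.00480 = 2.03 | 17% | 17.5% | 30% |
| 0.10 | 0.01450/0.00460 = 3.15 | 27% | 26.1% | 43% |

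The ratios at C = 0.5 are 0.00745/0.004975 = 1.50, 0.01725/0.004875 = 3.54 and 0.0295/0.00475 = 6.21. At C = 1 the ratio is 1 and the rate returns to 5%. Comparing hospital-level change between arms, 4 against 4, kept type I error at 0.047 to 0.057 over the same ICCs at C = 0.8.

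**What baseline adjustment could gain.** Follow-up difference, 80% power, two-sided 5%.

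- SE = √[(2/4)(ICC + (1 − ICC)/100)]
- Unadjusted multiplier (noncentral t, 6 df): 3.367
- Adjusted multiplier (5 df): 3.514, applied to SE·√(1 − r²)
- r = ICC·C/(ICC + (1 − ICC)/100), the correlation of observed hospital means

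Example at ICC 0.05, C = 0.8: SE = √(0.5 × 0.0595) = 0.1725, so unadjusted 3.367 × 0.1725 = 0.58 SD. r = 0.04/0.0595 = 0.672, so adjusted 3.514 × 0.1725 × 0.740 = 0.45 SD.

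| ICC | unadjusted | C = 1.0 | C = 0.8 | C = 0.5 | C = 0.3 |
|---|---|---|---|---|---|
| 0.01 | 0.34 | 0.30 | 0.32 | 0.34 | 0.35 |
| 0.05 | 0.58 | 0.33 | 0.45 | 0.55 | 0.59 |
| 0.10 | 0.79 | 0.33 | 0.56 | 0.73 | 0.79 |

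**The case against.** The strongest reply is that Section 4.1 does not assign the paired tests to records. The study also measures staff before and after training on coded forms, and a dependent t-test or sign test suits those if the codes link a person's forms. Between-arm tests and a clustered regression are planned alongside. All of this stands, and it limits the point to two gaps: the paired tests are not confined to linked data, and no model is named as the one that estimates the training effect.

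Four stronger readings are tempting and are not supported:

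- That the primary data cannot be validly analysed under this plan. Only the within-group tests fail, and only on records. The multi-level regression remains available.
- That the baseline audit is thrown away. The between-arm tests at each occasion do not use it, but the regression's terms are unstated. Its use is unspecified, not excluded.
- That false pairing causes the inflated error. It makes the p-value arbitrary; the inflation comes from ignoring hospital-by-occasion variation.
- That the feasibility study makes the same mistake. Section 3.1.5 does not apply its dependent t-test to records; for audit scores it specifies an agreement coefficient between raters. Section 3.1.1 already accepts that change there cannot be credited to training alone.

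**Conclusion.** The point holds in this limited form. As written, Section 4.1 allows paired tests on records that have no pairs, for part of the primary outcome, and gives within-arm tests the same standing as the analyses that compare arms. This part rests on the documents alone.

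The 25% and 16% figures follow from arithmetic for equal change in both arms at the stated power. The 7% to 27% range depends on the assumed ICC and an autocorrelation of 0.8: it is larger at lower autocorrelation and disappears at 1.0. The precision gain from baseline is also conditional. It is large when hospitals are stable over time, and nil or slightly negative at an autocorrelation of 0.3 for ICC 0.05 or 0.10, or at 0.5 and below for ICC 0.01. It is therefore a possible benefit, not the ground for the change.

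**What to change.** In Section 4.1:

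1. Restrict the paired tests to staff questionnaires linked by code, as description only, and state that each person keeps one code across occasions. Do not use them on records.
2. Name the multi-level model as the sole estimator of the training effect on records, in one of two forms:
   - (a) all occasions as outcomes, with arm, occasion, arm-by-occasion and ward as fixed effects, hospital and hospital-by-occasion as random effects, and the effect read from the arm-by-occasion contrast; or
   - (b) follow-up occasions only as outcomes, with the hospital's baseline mean as covariate.

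   The two should not be combined, because baseline would then be both outcome and covariate.
3. Use small-sample degrees of freedom for 8 hospitals.
4. For linked staff scores, model the follow-up scores with the individual's baseline score as covariate and staff member nested in hospital as random effects.

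The cost is revised wording and slightly more modelling, plus 1 degree of freedom if form (b) is chosen. No new data are needed, provided that the staff codes persist over time.

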#### ***3.2.2.2 Sample size calculation***

It is anticipated that a 20% (8) sample of 40 district hospitals will allow the outcomes to be generalised to the other hospitals. In their study, Zegers et al. (2007) reviewing patients records in Dutch hospital, a random sample of 20% of the hospitals was selected and the results were

generalized. At each hospital all the relevant health professionals will be included in the training so the sample will be one of convenience. The primary outcome of this study will be the improved interprofessional practice within the district hospitals and comprehensiveness of the patients' records demonstrated by the scores. A sample size calculation will be done once the needed tools have been finalised and the mean and standard deviation calculated during a feasibility study. However as multi-level regression analysis will be done to account for the effect of clustering, a sample of 800 patients records (100 from each hospital) should allow for the analysis of at least 80 variables. This is a large number but, as it is anticipated that the effect size will be small due to the presence of so many confounding variables, a large sample size will be required to prevent a Type II error from occurring.

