### ***3.2.2.3 Recruitment and sampling method***

#### **District hospitals**

Cluster random sampling will be used by a blinded person to select the district hospitals within 40 districts of four provinces. It is anticipated that eight district hospitals will participate in this study. The sample will include Gahini hospital, Kiziguro hospital, Nemba hospital, Rutongo hospital, Remera Rukoma hospital, Nyanza hospital, Byumba hospital, and Ruhango hospital. The same individual will randomly allocate four hospitals on the experimental arm and other four hospitals on the comparator arm. The experimental hospitals will include: Gahini hospital, Nemba hospital, Rutongo hospital, and Remera Rukoma hospital. The comparator hospital will be composed of Kiziguro hospital, Ruhango hospital, Byumba hospital, and Nyanza hospital.

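### Balance of diagnosis between arms is checked by a record-level chi-square that ignores hospital allocation and uses no outcome data; adjustment for ward or diagnosis is not pre-specified

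*Combined protocol and SAP*

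**What the plan says.** Section 4.1 (Data analysis) mentions diagnosis in two consecutive sentences. The first plans a "Chi-square test to ensure that there is no association between diagnosis and groups". The second says: "If necessary, sub-group analysis will be performed post-hoc to explore the impact of diagnosis on the outcome measures". No significance level, list of categories, audit occasion or allowance for clustering is given for the test. Nothing says what would make the sub-group analysis necessary.

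The same section says that "multi-level regression analysis will be done to control for the effect of clustering". It lists no covariates. Section 3.2.2.2 (Sample size calculation) expects that the "effect size will be small due to the presence of so many confounding variables" and says of the same regression that "a sample of 800 patients records (100 from each hospital) should allow for the analysis of at least 80 variables". None of those variables is named.

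On design, section 3.2.2.3 has one person "randomly allocate four hospitals on the experimental arm and other four hospitals on the comparator arm", and it plans 100 audited records per hospital at each of four occasions. Records are to be drawn by stratified sampling, with the strata not named. Section 2.1 describes the district hospitals outside Kigali as similar in their patients and conditions.

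**The concern.** A chi-square of diagnosis by arm takes two inputs, diagnosis and arm. Without the audit score it cannot show whether diagnosis is related to the score, nor whether training works differently by diagnosis. A non-significant result does not show balance, and a significant one does not show that the imbalance matters.

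The test also uses the wrong unit. Records from one hospital share that hospital's case mix, and hospitals, not records, are allocated. Ordinary differences between eight hospitals can therefore produce a significant result when allocation is sound.

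Neither step deals with an imbalance. Sub-group estimates chosen after the data are seen do not adjust the overall arm comparison, and they add unplanned results to a trial of eight hospitals. A link between type of patient and audit score is plausible from the instruments themselves: Appendix v scores items such as marital status, occupation and education, and Appendix vi counts items such as driving and paid employment. These apply differently to children and adults, yet all three ward types are pooled.

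**Working it through.** **The plan's own figures.** 0.20 × 40 = 8 hospitals; 8 × 100 = 800 records; 800 / 10 = 80 variables, which fits a ten-records-per-variable rule that the plan does not name. There is no stated figure for the diagnosis test to reproduce.

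**Step 1. How often the chi-square is significant from hospital case mix alone.**

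Inputs from the documents: 4 v 4 hospitals and m = 100 records per hospital at one occasion. Assumed: equally common categories (K of them), no arm effect, two-sided 5%, and a case-mix ICC from 0 to 0.10.

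Design effect: DE = 1 + (m − 1) × ICC. This gives 1 + 99 × 0.01 = 1.99; 1 + 99 × 0.02 = 2.98; 1 + 99 × 0.05 = 5.95; 1 + 99 × 0.10 = 10.9.

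Chance of significance ≈ P(χ² with K − 1 df > critical value / DE). For K = 3 this is exp(−5.99 / (2 × DE)):
- ICC 0.01: exp(−5.99 / 3.98) = 0.22
- ICC 0.05: exp(−5.99 / 11.9) = 0.60

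| Categories | ICC 0 | 0.01 | 0.02 | 0.05 | 0.10 |
|---|---|---|---|---|---|
| 3 | 0.05 | 0.22 | 0.37 | 0.60 | 0.76 |
| 5 | 0.05 | 0.31 | 0.53 | 0.81 | 0.93 |
| 10 | 0.05 | 0.48 | 0.77 | 0.97 | >0.99 |

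Simulation with hospital case mix drawn from a Dirichlet distribution (10,000 runs per cell) agrees within about 0.02. The test would be significant half the time at an ICC of 0.034 (3 categories), 0.018 (5) or 0.010 (10). If the four occasions were pooled (400 records per hospital, same case mix throughout), those values fall to 0.008, 0.005 and 0.003.

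**Step 2. What leaving diagnosis out of the model costs.**

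Assumed: residual SD 1, outcome ICC 0.02 (between-hospital variance 0.02 / 0.98 = 0.0204), case-mix ICC 0.05, diagnosis coefficients treated as known, and a t-test on hospital means with 8 − 2 = 6 df. Let b be the SD of the diagnosis effects on the score, in residual SDs.

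Variance of a hospital mean: adjusted, 0.0204 + 1/100 = 0.0304; unadjusted, 0.0304 + b² × 5.95/100. With four hospitals per arm, SE of the arm difference = √(2 × variance / 4).

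| b | Variance | SE | Power for a true difference of 0.4 SD |
|---|---|---|---|
| adjusted, any b | 0.0304 | 0.12 | 0.77 |
| 0.3, unadjusted | 0.0304 + 0.0054 = 0.0358 | 0.13 | 0.70 |
| 0.6, unadjusted | 0.0304 + 0.0214 = 0.0518 | 0.16 | 0.55 |
| 1.0, unadjusted | 0.0304 + 0.0595 = 0.0899 | 0.21 | about 0.35 |

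In simulation the type I error of this cluster-level test was about 0.05 with or without adjustment. The effect is on precision and on chance imbalance in the single realised allocation.

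**The case against.** Four points on the other side carry weight.

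- **The two sentences are not linked.** A reader might infer that a significant chi-square triggers the sub-groups and that a non-significant one ends the matter. Section 4.1 does not say so, and the sub-group sentence does look at outcomes. What stands is that the condition for the sub-groups is undefined and so is left to a choice made after the data are seen.
- **Adjustment is not excluded.** A reader might infer that the main comparison will be unadjusted. A regression meant to carry at least 80 variables foresees covariates, and diagnosis is neither named nor ruled out. The supportable statement is that adjustment for diagnosis or ward is not pre-specified.
- **The size depends on unknowns.** It would be too strong to say that the test will usually be significant. With three categories at one occasion it is significant in 22% of trials at an ICC of 0.01 and 37% at 0.02. Hospitals described as similar, and stratified sampling of records, both point to smaller case-mix differences; if the strata were wards, ward balance could be largely fixed by design.
- **A clustered balance test would hold about 5%.** That is true, and it would remove the false alarms. It would still use no outcome data, would have little power with eight hospitals, and would adjust nothing.

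There is also a fair objection to adjusting for recorded diagnosis. Appendix v item 14 asks only whether diagnosis is documented (yes, no or not applicable), and training may improve that. As an assumed illustration, if documentation rose from 80% to 95% and undocumented records scored 1 SD lower, adjusting for a not-stated category would remove about (0.95 − 0.80) × 1 = 0.15 SD of real effect. This changes the remedy, not the problem.

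**Conclusion.** The point holds, as something that should be changed. Without any assumption: the chi-square cannot establish balance, cannot show whether diagnosis matters for the score, and treats records as independent when hospitals are allocated; the sub-groups have no stated condition; and no covariate is pre-specified.

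The size rests on assumptions. For 3 to 10 categories, the false-alarm rate is about 20–50% at a case-mix ICC of 0.01 and 60–97% at 0.05, falling to 5% if there is no case-mix clustering. The loss of power runs from small (0.77 to 0.70) to large (0.77 to about 0.35) as the diagnosis effect rises from 0.3 to 1.0 residual SD, at the ICCs assumed in step 2. The plan itself expects a small effect, so lost precision matters.

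A reader might go further and conclude that the trial would give too many false-positive results. The calculations do not support that: a cluster-correct comparison keeps its type I error whether or not diagnosis is in the model.

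**What to change.** In section 4.1, delete the chi-square of diagnosis by group and the conditional post-hoc sub-group sentence. Replace them with text to this effect:

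- Ward of admission (orthopaedic/surgical, medical, paediatric) is a fixed effect in the multi-level model for the record-audit score in all analyses, whatever its distribution by arm.
- Ward and diagnosis are tabulated by arm without a test.
- One pre-specified arm-by-ward interaction is reported as exploratory.
- Broad diagnosis group may be added only if the auditor assigns it from information that does not depend on how completely staff documented the diagnosis. No not-stated category is used for adjustment.

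Ward suits this purpose because admission to one of the three wards is an inclusion criterion for records, so it is known for every record sampled. It varies within hospitals, so it uses no hospital-level degrees of freedom.

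Cost: one ward field must be added to the audit form, since Appendix v has none. No extra records or staff are needed. If ward turns out unrelated to the score, there is little gain and almost no loss: a simulation of adjustment for an unrelated category gave variance ratios of 0.98–1.00.
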